### Design, participants, and setting

This will be a survey of people receiving one of the two fact sheets. Around 790 patients who have recently seen their GP for back pain will be surveyed. Participants could receive a fact sheet via one of three methods. The first method is directly from their GP who prints and/or emails the sheet to their patient (GP-led access, Figure 1). The GP determines which sheet they will provide and so receipt of the JAMA or ACHSQ fact sheet is non-random.

[figure not shown]

**Figure 1.** GP-led access to back pain fact sheet. Appearance of the HealthShare sidebar where GPs can access fact sheets that are relevant to what is typed into consultation software. A clinician can print or email the sheet to their patient as they wish.

The second method is patient-led access to a back pain fact sheet via an SMS system called BetterConsult. BetterConsult invites a patient to receive a back pain fact sheet after they see their GP (Figure 2). Whether the patient receives the JAMA or ACHSQ fact sheet is determined randomly by the fact sheet distributor, HealthShare. Patients can view the sheet on their smartphone or print the sheet out and their GP will be notified. GPs can open and

discuss the fact sheet with their patient during the consult if they wish. Twenty-four hours after their consultation with the GP, HealthShare sends patients an SMS containing a link to the fact sheet.

[figure not shown]

The image shows a digital form with a white background and a thin black border. On the left side, there is a vertical purple bar. To the right of this bar, the text reads: "HealthShare offers a Low Back Pain Patient Information Fact Sheet. Would you like this to be sent to you via SMS after your appointment?". Below this text, there are two purple rectangular buttons. The left button is labeled "Yes" and the right button is labeled "No".

**Figure 2.** Patient-led access to back pain fact sheet. Patient opts to receive a fact sheet via SMS when they complete their details in a pre-consultation tool (BetterConsult).

The third method is via an advertisement on social media (Facebook, Twitter, and Instagram). The advertisement will invite people who have recently seen their GP for back pain to view a fact sheet and complete a short survey (See Appendix A).

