## Statistical analysis

Our primary analysis will compare the PrepDM scores in people exposed to the JAMA fact sheet vs the ACHSQ fact sheet, immediately after they have read the sheet. Assuming a mean difference of 6 points on a 100-point scale (ie 60 points in JAMA fact sheet group, 54 points in ACHSQ group, SD of 26) with 90% power, we require a sample size of 790. To account for anticipated uneven group size we will increase the minimum sample size to 1000.

For the secondary outcomes of management intentions, reassurance, and acceptability, we compare means and proportions where applicable in the whole sample and generate 95% confidence intervals.

---

 Western Sydney University. Human Research Ethics. Guidance on Reimbursements. 2020.

 Dhand, N. K., & Khatkar, M. S. (2014). Statulator: An online statistical calculator. Sample Size Calculator for Comparing Two Independent Means. Accessed 8 May 2023 at <http://statulator.com/SampleSize/ss2M.html>

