### Recruitment

Recruitment will happen from receipt of ethics approval (approximately April/May 2023) for a period of up to 12 months or until the target sample size of 1000 is achieved. Participants can opt in via the links on factsheets embedded in HealthShare consultation tools, or via an ad on social media.

GP users of the BetterConsult tool will be initially contacted about the interview/focus group study by email or newsletter from HealthShare. HealthShare regularly communicates with GP users of their tools in this way and have agreed to assist with recruitment. GPs who opt in to be contacted by investigators will receive an invitation email from the research team (Appendix E).

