| Update                                                                                             | 
This study is quasi randomised. Participants are allocated to intervention and control groups via three methods. The first method is based on GP discretion as to which study fact sheet they provide to their patient. The comparison of outcomes for people allocated to fact sheet interventions via this method is therefore non-random. The second allocation method is random. Based on a computerised random number list, a GP software provider will allocate access to either the intervention or control fact sheet, for one month at a time for the duration of the trial. The comparison of outcomes for people allocated to interventions via this method is therefore based on a randomised computer generated sequence.
 
The third allocation method will be random. Participants via social media advertisement will be allocated to either intervention or control fact sheet randomly.
                                                                                                                                                                                                                                                                                                                                                                                         |

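### The patient-led route randomises months rather than patients: the protocol does not state that unit, and the sizing and planned comparison make no allowance for it

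*Supplement*

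**What the plan says.** The latest protocol (Design, participants, and setting) has three access routes. GP-led receipt is non-random. For the patient-led SMS route: "Whether the patient receives the JAMA or ACHSQ fact sheet is determined randomly by the fact sheet distributor, HealthShare". The social media route is randomised in Qualtrics. The protocol concludes that the patient-led route allows a randomised comparison of the sheets, and it analyses the three routes separately as a sensitivity analysis. It does not mention months.

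The registry record in the same supplement (Study design, sequence generation, current update) describes the second route differently. The order is generated at random by computer, and under it "a GP software provider will allocate access to either the intervention or control fact sheet, for one month at a time". The update added the social media route and kept this monthly scheme.

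The protocol's Statistical analysis section sizes the primary comparison of PrepDM scores thus: "Assuming a mean difference of 6 points on a 100-point scale", with "54 points in ACHSQ group, SD of 26", and "with 90% power, we require a sample size of 790". The cited tool is a "Sample Size Calculator for Comparing Two Independent Means". The increase to 1000 is for uneven group sizes. Recruitment runs "for a period of up to 12 months or until the target sample size of 1000 is achieved".

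**The concern.** If everyone using the patient-led route in a given month is offered the same sheet, the comparison on that route is between months. Respondents from one month may resemble each other through season, the mix of practices or changes in recruitment. An analysis that treats them as independent understates the standard error and rejects too often.

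With about 12 units, time trends can also pass for a sheet effect. One source is built into the study. The nested ABACAD study changes the advertisement in successive periods in the same BetterConsult channel, and some periods offer a prize draw, which may change who responds. Nothing in the documents coordinates the advertising periods with the sheet months.

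At stake are the validity of the route-specific comparison that the protocol calls randomised and, to a lesser degree, the pooled primary comparison to which this route contributes.

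**Working it through.** **Step 1: reproduce the plan's figure.** Inputs from the protocol: difference 6, SD 26, power 90%. Alpha is not stated for the primary analysis; two-sided 0.05 is assumed.

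n per group = 2 × 26² × (1.960 + 1.282)² / 6² = 394.6, rounded up to 395, so 790 in total. This matches exactly (one-sided 0.05 would give 644). The 790 is an independent-respondent figure with no design effect.

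**Step 2: number of units.** One month at a time over up to 12 months gives about 12 units, assuming one switch for the whole system.

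**Step 3: patient-led route alone.** The documents give no ICC and no route size, so both are assumed: ICC 0.005–0.02, n respondents, 12 equal months (m = n/12).

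- Design effect: DE = 1 + (m − 1) × ICC
- Naive two-sided type I error = 2 × [1 − Φ(1.96/√DE)]

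| Patient-led n | m | DE | Naive type I error |
|---|---|---|---|
| 60 | 5.0 | 1.02–1.08 | 5.2%–5.9% |
| 120 | 10.0 | 1.05–1.18 | 5.5%–7.1% |
| 250 | 20.8 | 1.10–1.40 | 6.2%–9.7% |
| 500 | 41.7 | 1.20–1.81 | 7.4%–14.6% |

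Example, n = 500 and ICC 0.02: DE = 1 + 40.67 × 0.02 = 1.81; 1.96/√1.81 = 1.46; type I error 14.6%.

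Power for 6 points with n = 500, from a non-central t on 12 − 2 = 10 df, is 57% at ICC 0.005 and 41% at 0.02. Individually randomised respondents would give 73%. With n = 250 the corresponding figures are 35% and 29%, against 45%.

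**Step 4: pooled comparison of 1000.** Let n₁ be patient-led and treat the others as independent with equal groups. Only the share n₁/1000 is inflated:

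DE(pooled) = 1 + (n₁/1000) × (n₁/12 − 1) × ICC

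| n₁ of 1000 | DE (pooled) | Naive type I error | Power (normal approximation) |
|---|---|---|---|
| 100 | 1.004–1.015 | 5.0%–5.2% | 95% |
| 250 | 1.025–1.099 | 5.3%–6.2% | 95%–94% |
| 500 | 1.10–1.41 | 6.2%–9.8% | 94%–87% |

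Example, n₁ = 500 and ICC 0.02: DE = 1 + 0.5 × 40.67 × 0.02 = 1.41; effective N = 1000/1.407 = 711; power 87%.

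**Step 5: balance over time.** The registry states no restriction on the random list. If there were none, 12 months would split exactly 6:6 with probability C(12,6)/2¹² = 23%, and 8:4 or worse with probability 39%. This shows what an unrestricted list could do; it does not establish which list is used.

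**The case against.** The best defence is about scope. The 790 and 1000 cover all three routes pooled. The patient-led comparison alone is a sensitivity analysis, and no power is claimed for it. The registry says that social media was added because recruitment was too low, so the patient-led share may be small, and Step 4 shows that the pooled error then stays close to 5%. This stands, and it is why the results are shown by route size.

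Several stronger readings are tempting but not supported:

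- **That the plan's 90% power falls to 72%–49%.** Those figures follow at ICC 0.005–0.02 only if all 790 respondents are patient-led, which the three-route design rules out.
- **That the protocol states patient-level randomisation.** This is a natural reading, but the text names no unit. The fault is an omission that conflicts with the registry.
- **That switching is by calendar month, or from an unrestricted list.** The registry specifies neither.
- **That a distributor software change would be simple.** Nothing in the documents shows this.

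It can also be said that no separate analysis plan is shown, that cluster terms often belong there, and that the registry openly calls the study quasi randomised and discloses the monthly scheme. This lessens the weight of the missing period term. It does not settle what the unit is, and the sample size, which is in the protocol, rests on independent respondents.

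**Conclusion.** The point holds for the patient-led route. The registry makes the month the randomised unit, the protocol does not say so, and neither sizing nor planned comparison allows for it. Carried out as written, the route-specific comparison has standard errors that are too small, and sheet may be confounded with time, including the nested advertising periods.

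The mismatch of units needs no numerical assumption beyond one system-wide switch for the count of about 12; practice-by-practice switching would give more units, but the documents do not describe it. The size of the effect does depend on assumptions. At ICC 0.005–0.02 and 12 equal months, it ranges from minor (about 5%–7% type I error with 60–120 patient-led respondents) to serious (7%–15% with 500). For the pooled 1000 with 100–500 patient-led, type I error is about 5%–10% and power 95%–87%. The documents do not show that the primary analysis as a whole is invalid or has lost its stated power.

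**What to change.** 1. Reconcile the protocol's design section with the registry's sequence-generation entry, and state in both what is randomised, how often the sheet switches, and whether the switch is system-wide.
2. If monthly switching is kept, allocate the remaining months in consecutive two-month blocks, one month per sheet in random order. Record the advertising period in force in each month.
3. Analyse the patient-led data with month as the cluster, using a mixed model with a small-sample correction or a month-level test. Carry the same month term into the pooled analysis.
4. State that the 90% power assumes independent respondents, and restate it over a range of ICC and patient-led share.

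Randomising each patient when the SMS is sent would remove the problem for later recruits, but it is an option only if the distributor's system allows it.

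The cost is a constrained allocation list and some analysis wording. Intervals would be slightly wider and the stated power less favourable.

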#### Reason

We want to understand different survey advertising methods using fact sheets embedded in consultation software (BetterConsult provided by the company HealthShare) on recruitment rate.

### Recruitment

[Edit step 7](#)

#### Recruitment status

Not yet recruiting

#### Update

Recruiting

#### Reason

We added a new method of recruitment. Recruitment via a new method hasn't started. Recruitment via previously approved method has started.

#### Date of first participant enrolment

##### Anticipated

9/06/2023

##### Actual

#### Update

2/06/2023

#### Update

2/06/2023

#### Reason

We added a new method of recruitment via social media advertisement. The ethics amendment has been approved now.

#### Reason

We added a new method of recruitment via social media advertisement. The ethics amendment has been approved now.

#### Date of last participant enrolment

##### Anticipated

7/06/2024

##### Actual

#### Date of last data collection

##### Anticipated

7/06/2024

##### Actual

#### Sample size

##### Target

1000

##### Accrual to date

##### Final

#### Update

5224

#### Update

12

#### Reason

We added a nested study within the study to assess the effect of different survey advertising methods using fact sheets embedded in consultation software on recruitment rate.

#### Reason

We added a nested study within the study to assess the effect of different survey advertising methods using fact sheets embedded in consultation software on recruitment rate.

#### Recruitment in Australia

##### Recruitment state(s)

ACT,NSW,NT,QLD,SA,TAS,WA,VIC

### Funding & Sponsors

[Edit step 8](#)

#### Funding source category [1]

University

#### Name [1]

The University of Sydney, Faculty of Medicine and Health (Next Step Funding)

#### Address [1]

The University of Sydney  
NSW 2006  
Australia

#### Country [1]

Australia

#### Primary sponsor type

University

#### Name

The University of Sydney

#### Address

The University of Sydney  
NSW 2006  
Australia

#### Country

Australia

#### Secondary sponsor category [1]

None

#### Name [1]

N/A

**Address [1]** N/A

**Country [1]**

## Ethics approval

[Edit step 9](#)

**Ethics application status** Approved

**Ethics committee name [1]** The University of Sydney Human Research Ethics Committee

**Ethics committee address [1]** The University of Sydney  
NSW 2006  
Australia

**Ethics committee country [1]** Australia

**Date submitted for ethics approval [1]**

**Approval date [1]** 22/05/2023

**Ethics approval number [1]** 2023/179

## Summary

**Brief summary**

There is no rigorous evidence on the effects of back pain fact sheets among people seeking care for low back pain from their general practitioner. It is uncertain whether a fact sheet resource that focuses more on listing medical management options (JAMA Patient Page- low back pain), can increase a patient's preparedness for decision-making, compared with a resource that focuses on self-management (Australian Commission for Healthcare Safety and Quality Information for Patients Fact Sheet). Our primary aim is to compare preparation for decision-making among people seeking care for low back pain who are given one of two currently available fact sheets. Secondary aims are to examine management intentions, feelings of reassurance about serious pathology and the acceptability of the fact sheets to people seeking care for low back pain.

The study hypothesis is that a fact sheet resource which focuses more on listing medical management options (JAMA Patient Page- low back pain), can increase a patient's preparedness for decision-making more than a fact sheet that focuses on self-management (Australian Commission for Healthcare Safety and Quality Information for Patients Fact Sheet).

**Update**

There is no rigorous evidence on the effects of back pain fact sheets among people seeking care for low back pain from their general practitioner. It is uncertain whether a fact sheet resource that focuses more on listing medical management options (JAMA Patient Page- low back pain), can increase a patient's preparedness for decision-making, compared with a resource that focuses on self-management (Australian Commission for Healthcare Safety and Quality Information for Patients Fact Sheet). Our primary aim is to compare preparation for decision-making among people seeking care for low back pain who are given one of two currently available fact sheets. **Secondary aims are to understand recruitment processes and engagement with research fact sheets**, examine management intentions, feelings of reassurance about serious pathology and the acceptability of the fact sheets to people seeking care for low back pain.

The study hypothesis is that a fact sheet resource which focuses more on listing medical management options (JAMA Patient Page- low back pain), can increase a patient's preparedness for decision-making more than a fact sheet that focuses on self-management (Australian Commission for Healthcare Safety and Quality Information for Patients Fact Sheet).

**Reason** **Added a new method of recruitment**

**Trial website**

**Public notes**

**Private notes**

## Contacts

[Edit step 10](#)

